## Assessment of the causal relationship of adverse events

The investigator analyzes the correlation between adverse events and the investigational drug based on the established criteria, categorizing them into five classes: 'definitely related, probably related, possibly unrelated, definitely unrelated, and unable to determine.' Adverse events classified as 'definitely related, probably related, and unable to determine' are counted as related to the investigational drug.

### Criteria for determining the relationship between adverse events and investigational drug

- Is there a reasonable temporal relationship?
- Does it conform to known types of adverse reactions?
- Do adverse events disappear or lessen after discontinuation or dose reduction?
- Do adverse events recur after re-administration?
- Is there a possibility of other causes for the adverse events?

### Criteria for determining the relationship between adverse events and investigational drug

1. Definitely related:

- Reasonable temporal relationship+
- Conforms to known types of adverse reactions+
- Adverse events disappear or lessen after discontinuation or dose reduction+
- Adverse events recur after re-administration+
- There are other reasonable explanations -

1. Possibly related:

- Reasonable temporal relationship+
- Does it conform to known types of adverse reactions ±?
- Do adverse events disappear or lessen after discontinuation or dose reduction ±?
- Do adverse events reappear after re-administration of the drug?
- Is there a possibility that other reasons caused the adverse events ±?

1. Possibly unrelated:

- Reasonable time relationship -
- Does it conform to known types of adverse reactions -
- Do adverse events disappear or lessen after discontinuation or dose reduction ±?
- Do adverse events reappear after re-administration of the drug?
- Is there a possibility that other reasons caused the adverse events ±?

1. Definitely unrelated:

- Reasonable time relationship -
- Does it conform to known types of adverse reactions -
- Do adverse events disappear or lessen after discontinuation or dose reduction -
- Do adverse events reappear after re-administration of the drug -
- Is there a possibility that other reasons caused the adverse events +

1. Unable to determine: necessary evaluation data is unavailable

## Assessment of the severity of adverse events

The severity of adverse events (AEs) will be evaluated according to CTCAE v5.0 (see [Appendix 1](#附录一) ). If an AE occurs that is not within the range specified by this standard, the severity will be assessed using the following Table 3:

**Table 3 Adverse Event Severity Rating Scale for Events Not Specifically Listed in CTCAE**

| Level | Severity |
| --- | --- |
| 1 | Mild; asymptomatic or mild symptoms; clinical or diagnostic observation only; or no intervention required |
| 2 | Moderate; requires minimal, local, or non-invasive intervention; or age-appropriate instrumental activities of daily living are limited ^a^ |
| 3 | Severe or medically significant but not immediately life-threatening; requires hospitalization or prolongation of existing hospitalization; disability; or limitations in self-care activities of daily living ^b, c^ |
| 4 | Life-threatening consequences, or requiring emergency treatment ^d^ |
| 5 | Deaths related to adverse events ^d^ |

CTCAE Common Terminology Criteria for Adverse Events.=

a. Instrumental activities of daily living refer to activities such as cooking, shopping for groceries or clothes, making phone calls, and managing finances;

b. Examples of activities of daily living include bathing, dressing, eating, using the toilet, and taking medication, which are activities that non-bedridden patients can engage in;

c. If an event is classified as a 'serious medical event,' it must be reported as an SAE as described in section 8.7.2;

d. Grade 4 and 5 events must be reported as SAEs (please refer to Section [8.7.2](#_严重不良事件的报告) for reporting guidelines).

## Recording and reporting of adverse events and serious adverse events

### Recording and reporting of adverse events

During the study period, all AEs will be recorded until 60 days after the last administration of the investigational drug or the start of a new antitumor therapy, whichever occurs first. Adverse events should be described using a single diagnosis (rather than specific underlying symptoms and signs) whenever possible, including laboratory abnormalities that constitute AEs. When a definitive diagnosis cannot be made, each sign or symptom should be recorded as an independent adverse event.

After signing the informed consent form, adverse events should be investigated through non-leading questions directed at the subjects during the screening process and at each visit during the study. Methods for identifying adverse events also include active reporting by patients between the screening process or visits, or obtaining information through physical examinations, laboratory tests, or other assessments. Each adverse event should be evaluated as thoroughly as possible to determine:

- Severity grading (CTCAE v5.0) (see Section 8.6)
- Duration (start and end dates)
- Relationship to study treatment (the reasonable possibility that the AE is related to the study treatment) (see Section 8.5)
- Measures taken regarding the study or study treatment (none, dose adjustment, temporary interruption of treatment, permanent discontinuation of treatment, unknown, not applicable)
- Whether medication or treatment was administered (no concomitant medication/non-drug treatment, concomitant medication/non-drug treatment)
- Outcomes (not recovered/not relieved, recovered/relieved, in recovery/in relief, recovery/relief with sequelae, death, unknown)
- Whether it is a serious adverse event

In accordance with Chinese GCP regulations, all AEs occurring during the clinical research process, regardless of whether they are suspected to be related to the investigational drug, should be addressed with the following measures:

1. The investigator should immediately take appropriate protective measures for the subjects to ensure their safety; If concomitant medications or non-drug treatments are administered, this measure should be recorded in the adverse event CRF;
2. If the study is terminated, the investigator should also regularly check the subjects and fill in the termination date (the date of stopping the administration of the investigational drug), the reason for termination, and the detailed process in the CRF;
3. The investigator should follow up on all occurring AEs until any of the following situations occur:

- AE resolves or improves to baseline level or better;
- The investigator confirms that the event is stable and is not expected to improve further;
- Subject death;
- The subject has lost contact or withdrawn consent;
- The investigator confirms that the AE is unrelated to the study treatment;
- The subject has started a new antitumor therapy.

Any AE should be documented in detail on the CRF, and any changes in severity, suspected relationship to the study treatment, required therapeutic interventions, and outcomes should be assessed at each visit.

### Reporting of serious adverse events

Collect information on all SAEs and record it on the serious adverse event report form; To provide a comprehensive clinical report, all applicable sections of the form must be completed. Investigators must assess and document the relationship between each SAE and each specific study treatment (if more than one study treatment is involved), and submit the completed and signed form to the relevant national regulatory authorities and ethics committee within 24 hours. The original SAE report form and fax confirmation must be kept in the investigator's files at the research center.

Follow-up information should be sent to the same contact who received the original SAE report form, using a new SAE report form, indicating that this is follow-up information regarding the previously reported SAE, and providing the date of the original report. Regardless of when it occurs, the recurrence, complications, or progression of each initial event should be reported as follow-up information for that event. The follow-up information should describe whether there was relief or continuation of symptoms, whether treatment was received, how the treatment was administered, and whether to continue or withdraw from the study.

### Reporting and tracking of pregnancy

#### Pregnancy in female subjects

Fertile female patients who refuse to take effective contraceptive measures are prohibited from enrolling in this trial. If a female patient becomes pregnant during the study or within 60 days after the last dose of the investigational drug, the investigator should be notified immediately. The investigator should immediately (i.e., within 24 hours of learning of the pregnancy) complete the pregnancy report form and submit it to the relevant national regulatory authorities and the ethics committee. The investigator should immediately discontinue the investigational drug and discuss the risks of pregnancy and potential effects on the fetus with the subject. Follow-up for the pregnancy will continue until three months after the estimated date of delivery to determine outcomes, including spontaneous or voluntary termination of pregnancy, details of birth, any occurrence of birth defects, congenital anomalies, or maternal and/or neonatal complications, with follow-up for the newborn lasting at least three months. Any SAE related to pregnancy (such as events in the fetus/newborn or events occurring in the mother during or after pregnancy) should be recorded on the AE page of the CRF and reported promptly.

#### Pregnancy of female partners of male subjects

If the spouse of a male subject becomes pregnant during the study or within 60 days after the last dose of the investigational drug, the investigator should be notified immediately, and the investigator must report to the relevant national regulatory authorities and ethics committee within 24 hours of learning about the pregnancy. The investigator will provide information regarding the risks of pregnancy and potential effects on the fetus, and follow-up on the pregnancy status must be conducted as much as possible.

#### Miscarriage

All spontaneous abortions should be classified as SAEs, recorded on the AE page of the CRF, and reported immediately (i.e., within 24 hours of knowledge of the event).

#### Congenital Anomalies/Birth Defects

Any congenital anomalies/birth defects in infants born to female patients or female partners of male subjects who have been exposed to the investigational drug should be classified as SAEs, recorded on the AE page of the CRF, and reported immediately (i.e., within 24 hours of knowledge of the event).

## Adverse Event Recording Procedures

When recording AEs on the AE page of the CRF, investigators should use accurate medical terminology/concepts and avoid colloquialisms and abbreviations.

In the event field of the AE page in the CRF, only one AE term can be filled in.

### Infusion-related reactions

Adverse events (AEs) that occur during the administration of the investigational drug or within 24 hours after administration and are judged to be related to the infusion of the investigational drug should be recorded as diagnostic results on the AE page of the CRF (e.g., infusion-related reactions). Ambiguous terms, such as 'systemic reactions,' should be avoided whenever possible. If a subject experiences both local and systemic reactions after administration of the same dose of the investigational drug, each reaction should be recorded separately on the AE page of the CRF.

### Diagnosis and signs and symptoms

In addition to individual signs and symptoms, the AE page of the CRF should also record diagnostic results (if known), such as recording liver failure or hepatitis, rather than jaundice, asterixis, and elevated transaminases. However, if a single diagnosis cannot be made for a set of signs and/or symptoms at the time of reporting, each event should be recorded individually on the AE page of the CRF. If a diagnosis is subsequently clarified, all events previously based on the symptoms and signs of that diagnosis should be retracted and replaced with a single AE report based on the confirmed diagnosis, with the event start date being the start date of the initial symptom of the final diagnosis.

### adverse events secondary to other events

In general, AEs that are secondary to other events (such as cascade events or clinical sequelae) should have their primary cause determined, except for severe or serious secondary events. If the secondary adverse event (AE) is clinically significant and both events occur independently in terms of timing, the secondary event should be recorded as a separate event on the AE page of the Case Report Form (CRF). For example:

- In healthy adults, if vomiting leads to mild dehydration and no other treatment is required, only vomiting should be reported on the CRF;
- If vomiting leads to severe dehydration, these two events should be reported separately on the CRF;
- If severe gastrointestinal bleeding leads to renal failure, these two events should be reported separately on the CRF;
- If dizziness leads to a fall, resulting in a fracture, it should be reported as three separate events on the CRF;
- If neutropenia leads to infection, these two events should be reported separately in the CRF.

If it is unclear whether there is a relationship between the events, all AEs should be recorded separately on the AE page of the CRF.

### Persistent or recurrent adverse events

A persistent AE refers to an AE that continues without relief between assessment time points for each subject. Such events need to be recorded only once on the AE page of the CRF. At the time of the initial report of the event, the initial severity (grade or level) of the event should be recorded. If the persistent AE worsens, the maximum severity should be recorded on the AE page of the CRF. If the AE meets the criteria for SAE, the investigator must report it immediately (within 24 hours of becoming aware of the worsening event). Update the AE page of the CRF by changing the severity of the event from 'non-serious' to 'serious', providing the date of event escalation, and filling in all data related to the SAE.

Recurrent AEs refer to AEs that have resolved at the current assessment point compared to the previous assessment point but then recur. Each recurrence of an AE should be recorded separately on the AE page of the CRF.

### Abnormal laboratory test values

Not every abnormal laboratory test value qualifies as an AE. Abnormal laboratory test results must be reported as AEs when they meet any of the following criteria:

- Accompanied by clinical symptoms;
- Leading to changes in study treatment (e.g., dose adjustment, treatment interruption, or termination of treatment);
- Requires medical intervention (e.g., potassium supplementation for hypokalemia) or changes in concomitant medication;
- The investigator considers it clinically significant.

If a clinically significant laboratory abnormality is a sign of a disease or syndrome (e.g., ALP and bilirubin > 5 ULN related to cholestasis), only the diagnosis (i.e., cholestasis) needs to be recorded on the AE page of the CRF.×

If a clinically significant laboratory test result abnormality is not indicative of a specific disease or syndrome, the abnormal result itself should be recorded on the AE page of the CRF, accompanied by a description indicating whether the result is above or below the normal range (e.g., 'hyperkalemia' instead of 'potassium abnormality'). If an abnormal laboratory test result is defined as per the standard and can be accurately described using a clinical term, that clinical term should be recorded as an AE. For example, if serum potassium rises to 7.0 mEq/L, it should be recorded as 'hyperkalemia.'

If the same clinically significant abnormal laboratory test result is observed between visits, it should only be counted once on the AE page of the CRF (for detailed information on recording persistent AEs, please refer to Section 8.8.4 ).

The investigator is responsible for reviewing all laboratory test results. For laboratory abnormalities that meet the criteria for adverse events, follow-up should continue until normalization or baseline levels are achieved and/or there is a reasonable and sufficient explanation.

Laboratory abnormalities that do not meet the definition of adverse events should not be reported as AEs. CTCAE graded events of grade 3 or 4 (severe) do not automatically qualify as SAEs unless they meet the definition of serious adverse events and/or are determined by the investigator to be serious adverse events.

### Abnormal vital sign values

Not every abnormal vital sign value qualifies as an AE; when the results of vital sign examinations meet any of the following criteria, they must be reported as AEs:

- Accompanied by clinical symptoms;
- Leading to changes in study treatment (e.g., dose adjustment, treatment interruption, or termination of treatment);
- Requiring medical intervention or changes in concomitant medication;
- The investigator considers it clinically significant.

The investigator is responsible for reviewing all vital sign examination results.

If an abnormal vital sign examination result of clinical significance indicates a certain disease or syndrome (e.g., hypertension), only the diagnosis (i.e., hypertension) needs to be recorded on the AE page of the CRF.

If the same clinically significant abnormal vital sign examination result is observed at each visit, it should not be repeatedly recorded on the AE page of the CRF unless there is a change in the underlying cause (for details on recording persistent AE, please refer to Section 8.8.4 ).

### Abnormal liver function test results

Elevated ALT or AST (3ULN) and elevated total bilirubin (2ULN) or clinical jaundice, but without cholestasis or other causes of hyperbilirubinemia, should be considered indicative of severe liver injury (as defined by the Haisch criteria). Therefore, when any of the following situations occur, the investigator must report it as an SAE:>×>×

- During treatment, if ALT or AST is 3 ULN, accompanied by total bilirubin 2 ULN;>×>×
- ALT or AST of 3 ULN occurring during treatment, accompanied by clinical jaundice.>×

The most appropriate diagnosis or laboratory abnormality (if a clear diagnosis cannot be made) will be recorded as an SAE in the AE page of the CRF and reported immediately (i.e., reported within 24 hours of becoming aware of the event).

### Death

In this study protocol, death is considered an efficacy endpoint. Deaths occurring within the AE reporting period specified in the study protocol, if the investigator determines the cause of death to be tumor progression, should be recorded in the CRF under the section for deaths attributed to disease progression. All other study-related deaths, regardless of whether they are related to the investigational drug, must be recorded on the AE page of the CRF and reported immediately.

Death should be considered an outcome rather than a separate event. Events or conditions leading to a fatal outcome should be recorded as a single medical concept on the AE page of the CRF. Generally, only one such event should be reported. The term 'sudden death' is used only for deaths that are abrupt and unexpected, with a presumed cardiac cause. If the cause of death is unknown, or cannot be determined at the time of reporting, it should be recorded as 'cause of death unknown' on the AE page of the CRF. If the cause of death is clarified later (e.g., after autopsy), 'cause of death unknown' should be changed to the clarified cause of death.

Deaths attributed to tumor progression that occur during the survival follow-up period should be recorded in the death CRF attributed to disease progression.

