Safety profile, the incidence of TEAE in the 0.2g group is 96.2%, and in the 0.3g group is 98.1%; The incidence of SAE in the 0.2g group is 39.6%, and in the 0.3g group is 22.2%; The incidence of TEAE leading to death in the 0.2g group was 15.1%, and in the 0.3g group was 13.0%; The most frequently occurring SOC of TEAE in both groups was 'Skin and Subcutaneous Tissue Disorders' (incidence in the 0.2g group was 75.5%, and in the 0.3g group was 83.3%), with the PT being Palmoplantar Erythrodysesthesia Syndrome (incidence in the 0.2g group was 62.3%, and in the 0.3g group was 61.1%). The overall safety and tolerability of donafenib 0.2g and 0.3g were good.

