## 3.4 DLT Assessment and Judgment Criteria

DLT is defined as any of the following adverse events, unless the investigator determines that it is definitely related to the study progression or caused by other external factors, it will be considered as DLT:

Hematologic Toxicity:

- - - 1. Grade 4 neutropenia lasting more than 7 days.
      2. Febrile neutropenia [defined as an absolute neutrophil count (ANC) < 1×10^9^ /L, accompanied by a single temperature reaching 38.3℃ or a temperature of 38℃ persisting for more than one hour].
      3. Grade 3 neutropenia with infection.
      4. Grade 3 thrombocytopenia with severe uncontrollable bleeding events.
      5. Grade 4 thrombocytopenia.
      6. Grade 4 anemia (life-threatening).
      7. Grade 3 or 4 lymphopenia with opportunistic infections.

Non-hematologic toxicity:

Skin reactions: severe hand-foot skin reaction (HFSR) or other skin adverse reactions that persist for >2 weeks or occur a second time despite appropriate intervention.

Blood pressure: persistent/recurrent systolic blood pressure ≥160 mmHg or diastolic pressure ≥100 mmHg on the second occurrence, and remains uncontrolled despite aggressive antihypertensive treatment. (Persistent/recurrent blood pressure ≥160/100 mmHg refers to measurements of ≥160/100 mmHg taken at least twice with an interval of 24 hours, with each measurement taken after the subject has been seated and resting quietly for more than 5 minutes.) At least 1 week of antihypertensive medication is allowed before the second recorded hypertension event occurs.

Cardiac contractile function: First occurrence of LVEF decrease >10%, or LVEF value <40%.

Gastrointestinal system: Grade 4 diarrhea, or Grade 3 diarrhea lasting >24 hours despite active antidiarrheal treatment, or occurrence of two episodes of Grade 3 diarrhea regardless of duration; Occurrence of ≥ grade 3 nausea and vomiting despite adequate/maximum medical intervention and/or preventive measures.

Absolute QTcB ≥500 msec (at two consecutive time points).

Other Grade 4 or higher adverse events.

Grade 3 or higher immune-related adverse events (irAE).

Other Grade 3 toxic effects, except for laboratory abnormalities that recover to Grade 2 (inclusive) or below within 3 days (asymptomatic and not requiring medical intervention).

In addition to the above events, DLT events also include any level of toxic reaction that the investigator considers necessitating the subject's withdrawal from the study.

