**Events that do not meet the definition of an AE include:**

1. Medical or surgical procedures (e.g., endoscopy, appendectomy); the conditions leading to these procedures should be recorded as AEs;
2. Conditions of hospitalization that did not result in adverse medical events (due to social insurance and/or convenience hospitalization);
3. Planned hospitalization required by the protocol (e.g., for the use of the investigational drug);
4. Expected day-to-day fluctuations of pre-existing diseases or conditions present or detected at the start of the study, but without exacerbation;
5. Expected progression, signs, or symptoms of the disease/disorder being studied, unless the severity of the subject's condition exceeds expectations or progresses more rapidly.

Adverse signs, symptoms, or medical conditions that existed at the time of signing the informed consent form should be recorded as medical history.

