## Serious Adverse Events (SAE)

Meets any of the following criteria:

1. Results in death (i.e., AE causes or leads to death);
2. Is life-threatening (i.e., the investigator believes that the AE places the patient at immediate risk of death);

Note: The term 'life-threatening' refers to the risk of death at the time of the event, and does not imply that a more severe event would lead to death.

1. Results in permanent or significant disability or functional impairment;

Note: The term 'disability' refers to a severe impairment of an individual's ability to perform normal life functions. This definition does not include clinically insignificant events, such as simple headaches, nausea, vomiting, diarrhea, influenza, and accidental injuries (e.g., ankle sprains), which may affect daily functioning but do not result in a significant loss of function.

1. Causing congenital malformations/birth defects;
2. Requires hospitalization or prolongation of current hospitalization ;

Note: Generally speaking, hospitalization refers to a patient being observed in a hospital or emergency department (typically at least overnight) and/or receiving treatment that is not suitable for a doctor's office or outpatient department.

Hospitalization for the following reasons is not reported as an AE, but the reason for hospitalization must be clearly documented in the medical record:

1. Planned hospitalization as specified in the study protocol (e.g., for administration of the investigational drug, or for efficacy assessment of this study);
2. Routine treatment or monitoring for the study indication;
3. Hospitalization solely due to related tumor progression;
4. Hospitalization due to pre-existing conditions, but must meet all of the following criteria:
   - - Hospitalization planned prior to the study, or hospitalization for elective surgery due to predictable disease progression during the study;
     - Subjects did not experience any AEs or disease progression.
5. Social reasons and treatment delays in the absence of deterioration in the patient's general condition.

The following hospitalization situations will not be considered SAEs but should be reported as AEs:

1. Subjects hospitalized due to the need for outpatient medical care outside of normal clinic hours.

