2. Other important medical events that require medical and scientific judgment to determine whether expedited reporting is necessary, such as important medical events that may not immediately threaten life, result in death, or require hospitalization, but if medical measures are needed to prevent one of the above situations from occurring, are typically considered serious. For example, important treatments in the emergency room or allergic bronchospasm occurring at home, cachexia or seizures not requiring hospitalization, and the development of drug dependence or addiction, etc.
3. SAE as defined in the protocol:
4. Potential drug-induced liver injury, including elevated ALT or AST levels, accompanied by elevated bilirubin levels or clinical jaundice, as specifically defined in the Hais' criteria (see Section 8.8.7 for details).
5. AE caused by drug overdose, regardless of the CTCAE grading level.

If tumor progression (including fatal outcomes) is recorded using appropriate methods (such as according to the mRECIST criteria for solid tumors), it is not reported as a serious adverse event.

In cases where treatment is based on outpatient emergency visits that do not result in hospitalization and the events do not meet any of the SAE definitions provided above, they are not reported as serious adverse events.

The terms 'serious' and 'severe' are not synonymous; 'severity' and 'seriousness' are also not synonymous. Severity refers to the intensity of the AE (as determined by CTCAE v5.0; see [Section 8.6](#_不良事件严重程度评价) ); The medical significance of the event itself may be relatively minor (for example, severe headache with no other findings).

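### Sections 8.2 and 8.8.8 apply different tests to deaths from tumor progression, so a death without documented progression can leave the fatal-AE count on the investigator's attribution alone

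*Protocol*

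**What the plan says.** Three places in the protocol decide how a death from the underlying cancer is handled.

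- **Section 8.8.8 (Death).** For a death inside the AE reporting period: "if the investigator determines the cause of death to be tumor progression, should be recorded in the CRF under the section for deaths" (the section meant is the one for disease progression). The other study-related deaths, whether or not related to the drug, "must be recorded on the AE page of the CRF and reported immediately". The section names no scan, response criterion or other record that must support the attribution.
- **Section 8.2 (Serious Adverse Events).** One SAE criterion reads "Results in death (i.e., AE causes or leads to death"). The section then gives an exemption: "If tumor progression (including fatal outcomes) is recorded using appropriate methods (such as according to the mRECIST criteria for solid tumors"), the event is not reported as an SAE.
- **Section 8.1 (events that are not AEs).** Expected progression of the disease is not an AE, "unless the severity of the subject's condition exceeds expectations or progresses more rapidly".

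The period to which 8.8.8 applies is itself stated in two ways. Section 8.7.1 says "all AEs will be recorded until 60 days after the last administration of the investigational drug" (or until new antitumor therapy, if earlier). Sections 4.3.3 and 6.5.1 and note 20 of the trial flowchart use 30 days.

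**The concern.** The test in 8.2 is whether progression was recorded. The test in 8.8.8 is what the investigator believes caused the death. They give the same answer when progression has been documented and different answers when it has not. Site staff cannot follow both for an unscanned patient whose death is put down to tumor.

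Such patients are plausible. Scans are 6 weeks apart during combination treatment (section 6.3) and 12 or 24 weeks apart in efficacy follow-up (6.5.2), so a death inside the window can come before any scan showing progression. The protocol itself lists gastrointestinal bleeding, bilirubin and transaminase elevation, and immune-related liver dysfunction among the toxicities to be managed (8.3 and 8.4). These can be hard to separate from advanced liver cancer. The study is single-center, open-label and single-arm (3.1), images are read at the center (9.3), and the protocol describes no independent review of cause of death.

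Adverse events and SAEs are a stated secondary endpoint (2.2). This is a data-capture rule, so an analysis limited to the AE page would not recover a fatal outcome entered elsewhere.

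**Working it through.** The protocol gives no figure to reproduce here. The check is a comparison of the rules, followed by the size of one reclassified death.

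**Step 1. Apply the rules to each kind of death inside the AE window.**

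| Death in the window | Sections 8.1 and 8.2 | Section 8.8.8 | Agree? |
| --- | --- | --- | --- |
| Attributed to tumor, expected progression, documented | Not an SAE | Progression section | Yes |
| Attributed to tumor, progression not documented | The condition of the 8.2 exemption is not met | Progression section; not among the deaths sent to the AE page and reported at once | **No** |
| Attributed to tumor, progression worse or faster than expected | Still an AE under 8.1 | Progression section, without the 8.1 limit | **No** |
| Cause unknown | Not covered by the exemption | AE page, entered as unknown cause | Yes |
| Attributed to another event | SAE | AE page and immediate report | Yes |

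The second row is the main conflict. The third is a smaller one of the same kind.

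**Step 2. Size of one reclassified death.** Inputs: n = 30 (section 3.2), assuming all 30 are treated and enter the safety set. With F fatal AEs the rate is F/30. Moving one death to the progression section gives (F − 1)/30, a change of 1/30 = 3.3 percentage points.

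Exact (Clopper-Pearson) 95% intervals, with lower limit the 0.025 quantile of Beta(x, n − x + 1) and upper limit the 0.975 quantile of Beta(x + 1, n − x):

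- 0/30 = 0% (0 to 11.6%)
- 1/30 = 3.3% (0.1 to 17.2%)
- 2/30 = 6.7% (0.8 to 22.1%)
- 3/30 = 10.0% (2.1 to 26.5%)

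One death moved turns 3/30 into 2/30, or 1/30 into none. The intervals overlap widely, but they describe sampling error only; they do not allow for a count that is too low because of how deaths were filed.

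**The case against.** The strongest reply is that the sections can be read together: 8.8.8 only says which CRF section holds the death, and 8.2 still decides whether it is an SAE. Section 8.8.8 does not say outright that progression deaths are exempt. That reading is possible, but 8.8.8 links the AE page and immediate reporting to the deaths left over after progression deaths are removed, and nothing tells the site to file an SAE for a death placed in the progression section.

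The second reply is that other rules catch much of what matters, and this largely stands. Life-threatening events and hospitalizations are SAEs in their own right (8.2). Transaminase elevation with raised bilirubin or jaundice must be reported within 24 hours (8.8.7). A death of unknown cause goes to the AE page (8.8.8). Overall survival counts death from any cause (7.4.2), so no death disappears from the trial. What remains exposed is mainly the fatal outcome of an event, and the death with no separately reported event before it.

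Four stronger readings are tempting and are not supported:

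- A reader might infer that 8.2 demands imaging. It asks for an appropriate method and offers mRECIST as an example, so the requirement is documentation.
- A reader might infer that treatment-related deaths will be filed as disease, or that reporting of the main safety signal will be delayed. The wording allows this for some deaths; nothing shows that it would happen.
- A reader might project a count from the account of study ZGDH1B: "The incidence of TEAE leading to death in the 0.2g group was 15.1" percent, which matches 8/53, and 30 × 8/53 = 4.5. The protocol does not say how that study classed progression deaths or what its event window was, and the treatment differed. Any share assumed to be relabelled would be arbitrary.
- A reader might extend the point to the DLT definition, which applies "unless the investigator determines that it is definitely related to the study progression or caused by other external factors". That clause requires a definite judgement and concerns toxicity in the first six subjects. It is a separate matter.

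**Conclusion.** The point holds as a conflict between two recording rules. A death in the AE window without documented progression does not meet the exemption in 8.2, yet 8.8.8 allows it to be entered as disease on attribution alone, and 8.8.8 also drops the limit in 8.1 to expected progression. The effect runs one way: it can only lower the fatal-AE count. Its size is 3.3 percentage points per death with 30 treated subjects, and the number of such deaths cannot be derived from the documents. The conclusion rests on reading the 8.2 exemption as conditional on a record of progression, and on reading 8.8.8 as withholding the AE page and immediate report from deaths attributed to progression. Both are the natural readings. It does not rest on any table being absent from the protocol, since table content may be set in the statistical analysis plan. This should be corrected, as there is no control arm against which a misattributed death would show.

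**What to change.** First make the AE window consistent across 8.7.1 (60 days) and 4.3.3, 6.5.1 and flowchart note 20 (30 days), because 8.8.8 takes its scope from it. Then amend 8.8.8 to say that:

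1. a death in the AE window goes only to the disease-progression section when progression has been documented as 8.2 requires, with a statement of how the 8.1 limit to expected progression applies;
2. every other death in the window is recorded on the AE page with the event that led to it and reported as an SAE;
3. all deaths in the window are summarised regardless of attributed cause.

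This changes recording and reporting only. The cost is a short text amendment, one summary of deaths, and a few extra SAE forms for deaths that may later be accepted as progression. It does not remove the investigator's judgement of cause or the reliance on local image reading; it ensures that a judgement without documentation no longer takes a death out of the safety data.
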